##### Traditional Chinese Medicine (TCM) Syndrome Score Scale

Syndrome is the objective basis of syndrome differentiation and treatment in TCM. The subjects of this study are mild insomnia patients with anxiety disorders, so the TCM syndrome score scale includes the insomnia part and depression part, the sum of the two is the total score. The syndrome scale with the characteristics of TCM theory is necessary to realize the standardization of TCM syndrome diagnosis and evaluation.

Except for laboratory tests, the primary and other secondary outcomes are detected at baseline and every four weeks. Laboratory data are tested at baseline and the 8^th^ week.

### Statistical analysis

Participants will complete relevant questionnaires and laboratory tests at the first visit. Researchers will guide to ensure the reliability and validity of the questionnaire; meanwhile, a sleep monitor will be completed before the treatment.

All observation results will be documented in the clinical observation forms. Missing data will be replaced according to the principle of LOCF (the last observation carried forward). At the same time, a computer database will be established. The obtained data will be input into the computer on the day of observation records. SPSS 21.0 will be used for statistical processing. Measurement data will be summarized by descriptive statistics (mean, standard deviation (SD), median and interquartile), count data use frequency tables (frequencies and percentages). Normal distribution test and homogeneity test of variance are performed on measurement data. The baseline characteristics of the two groups will be analyzed using independent samples *t* test or Mann-Whitney *U* test (if the distribution was not normal or the variance not homogeneous). If the baseline characteristics are imbalanced, covariance analysis is used to adjust the data. We will use an independent sample *t* test for comparison of between-group comparison and paired sample *t* test for comparison within each group after data meeting normal distribution test and homogeneity test of variance, otherwise using Mann-Whitney *U* test and Wilcoxon signed-rank test. The Pearson chi-square will be performed to compare count data. All statistical tests will be conducted at a 2-tailed significance level of 5%.

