### Randomization, allocation concealment

A random sequence list is generated using stratified block randomization design and SAS 9.4 (SAS Institute Inc., Cary, NC, USA). The sequence is stratified by gender and age. This trial has an independent statistician assigning the eligible patients to the corresponding intervention code based on the list, who is not be involved in recruitment, implementation, data collection, and data analysis of this trial. All of the random code information is kept by a certain person and stored in sealed opaque envelopes. When an eligible patient is enrolled in the group, the statistician will randomize the patient according to the above method, and the corresponding box with a wrist-ankle strap will be given to the researcher who will be responsible for informing patients the details about the implementation, the wrist-ankle straps used in both groups will have the same packaging. The allocation concealment procedure will not be exposed until the clinical trial is finished.

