### Sample size

PASS 11 software (NCSS, Kaysville, UT) was used to calculate the required sample size. The sample size calculation formula is as follows:
$$ {n}_t={n}_c=\frac{{\left({Z}_{1-\raisebox{1ex}{$\alpha $}\!\left/ \!\raisebox{-1ex}{$2$}\right.}+{Z}_{1-\beta}\right)}^2{s}^2\left(1+\raisebox{1ex}{$1$}\!\left/ \!\raisebox{-1ex}{$k$}\right.\right)}{{\left({\mu}_t-{\mu}_c\right)}^2} $$

Sample size calculation is based on the primary outcome, which is proposed to be the PSQI. Based on the preliminary experiments, the PSQI aggregate score of the acupressure wrist-ankle strap group was 6.125±2.93, and the PSQI aggregate score of the control group was 8.625±3.77. Two groups were 8 cases respectively. The combined standard deviation of the two groups was calculated to be 3.60. That is, in the formula, *μ*_*t*_=6.125, *μ*_*c*_=8.625, *k*=1, and *s*=3.60. In this study, *α*=0.05 and 1-*β*=0.9, therefore $$ {Z}_{1-\raisebox{1ex}{$\alpha $}\!\left/ \!\raisebox{-1ex}{$2$}\right.}= $$1.96, *Z*_1 − *β*_=1.28. Forty five patients are required for each group. Fifty-seven patients will be enrolled in each group after considering an estimated 20% dropout rate, giving a total of 114 patients.

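### The data choose the primary PSQI analysis: adjustment only if baseline looks imbalanced, and t test or Mann-Whitney by pretest. This forgoes precision and lets the estimated effect change.

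*Protocol article*

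**What the plan says.** All of the analysis rules are in the Statistical analysis section of the protocol article.

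- Baseline characteristics are compared between arms by t test or Mann-Whitney. Adjustment depends on what is found: "If the baseline characteristics are imbalanced, covariance analysis is used to adjust the data". The section does not say what counts as imbalanced or which covariates would enter.
- The between-group comparison is an independent-samples t test only "after data meeting normal distribution test and homogeneity test of variance". Otherwise it is Mann-Whitney. Paired tests within each arm are listed alongside.
- All tests are two-sided at 5%.

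Two other sections matter. The Primary outcome section has PSQI measured at baseline, at weeks 4 and 8, and at follow-up, so every patient has a baseline value. The randomisation section states: "The sequence is stratified by gender and age". Neither baseline PSQI nor the strata appear as fixed terms in the analysis.

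**The concern.** The article states these rules itself, so they are not detail left to an analysis plan that is not shown. Three things follow from them.

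1. Whether the primary comparison is adjusted, and for what, is settled only after data have been seen. In a randomised trial a baseline imbalance arises by chance. A significance test for it is a poor guide to whether a covariate is worth adjusting for; what matters is how strongly the covariate predicts the outcome.
2. The t test compares means and Mann-Whitney compares rank distributions. A pretest that picks between them can change the effect being estimated, whereas the sample size is built on a difference in means.
3. When baseline PSQI and the stratification factors are left out, the default t test carries outcome variance that could have been removed. If the strata are prognostic, its standard error is also too large for a stratified design.

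At stake are a single well-defined primary estimate and some precision.

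**Working it through.** **The plan's own figure.** The Sample size section gives "the PSQI aggregate score of the acupressure wrist-ankle strap group was 6.125±2.93" and "the PSQI aggregate score of the control group was 8.625±3.77", a difference of 2.5. It uses an SD of 3.60, and "In this study, *α*=0.05 and 1-*β*=0.9".

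- Stated formula: (1.96 + 1.28)² × 3.60² × 2 / 2.5² = 43.5, so 44 per arm.
- The t-based version gives 44.6, so 45 per arm, which is the stated figure.
- With 20% dropout: 45 / 0.80 = 56.25, so 57 per arm and 114 in total. This reproduces.

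**Gain from always adjusting for baseline PSQI.** The documents give no correlation r between baseline and follow-up PSQI, so it is bounded from the entry criterion.

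- Entry PSQI is 7–11. If the five scores are equally likely, the baseline SD is √2 = 1.41 (an assumption; the maximum possible is 2).
- r = slope × baseline SD / follow-up SD. Slope 0.5: 0.5 × 1.41 / 3.60 = 0.20. Slope 1: 1.41 / 3.60 = 0.39. So r is about 0.2–0.4.
- The variance factor is 1 − r², and the equivalent sample is 90 / (1 − r²), with 90 = 2 × 45 analysed.

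| r | Variance factor | 90 patients worth | Power at 45 per arm |
|---|---|---|---|
| 0 (unadjusted) | 1.00 | 90 | 90.9% |
| 0.2 | 0.96 | 94 | 92.0% |
| 0.3 | 0.91 | 99 | 93.2% |
| 0.4 | 0.84 | 107 | 94.9% |

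Power is by normal approximation with difference 2.5 and SD 3.60 × √(1 − r²).

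The choice of SD hardly matters here. The article says "The combined standard deviation of the two groups was calculated to be 3.60", but with equal arms of 8, √((2.93² + 3.77²)/2) = 3.38. With 3.38 the correlations are 0.21 and 0.42.

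**What the written rule delivers.** It was simulated at 45 per arm, taking imbalance to mean p < 0.05 for baseline PSQI (an assumption).

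- ANCOVA is triggered in about 5% of trials, so almost all of the gain is lost. At r = 0.3, simulated power is 89% under the rule and 92% with ANCOVA always.
- The pretests send about 13–15% of trials with truly normal data to Mann-Whitney.

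**Type I error of the written rule** (5,000 runs per setting, Monte Carlo error about 0.6 points).

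- Normal data, strata not prognostic: 5.1% at r = 0, 4.5% at r = 0.5, and 3.8% at r = 0.7 (an extreme value).
- Prognostic strata left out: 3.7–3.8%, or 3.1–3.7% with skewed data.
- ANCOVA with baseline and strata: 4.6–5.8% across all settings.

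For the strata alone there is a simple formula. If they explain a share v of the outcome variance, the true level of the unadjusted test is P(|Z| > 1.96/√(1 − v)): 4.8% at v = 0.02, 4.4% at 0.05, 3.9% at 0.10 and 2.8% at 0.20. The documents do not give v.

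**The case against.** **The error rate is not inflated.** A reader might infer that a data-driven analysis must produce excess false positives. The rule as written does not: its level is at or below 5%, and the pretest switch alone leaves it at 4.7–5.5% when strata are not prognostic. Inflation needs selective use of the undefined trigger. If the smaller p value were always taken, the level would be 6.0–7.5% (t or ANCOVA) or 6.8–8.2% (adding Mann-Whitney) for r of 0.2–0.5. No passage says this will happen, and the Blinding section blinds the data analysts, which limits choices made to favour one arm. This objection stands.

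**The trial is not left underpowered.** The unadjusted test is the basis of the sample size, and 45 per arm reproduces. Adjustment adds to the planned power and does not repair a shortfall. This also stands.

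**Four further inferences that the documents do not support.**

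- A high rate of false imbalance flags. Ten independent characteristics would give 1 − 0.95^10 = 40%, but the article gives no list or number.
- A switch to Mann-Whitney foreshadowed by the pilot SDs. Their variance ratio is (3.77/2.93)² = 1.66. With 8 per arm the F test gives p of about 0.52, and the same ratio at 45 per arm gives about 0.10.
- Baseline PSQI ignored altogether. Conditional adjustment is allowed; what is absent is unconditional adjustment.
- Within-arm tests offered as evidence of efficacy. They are only listed, and the Discussion frames the aim as comparing the two straps.

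None of this defends choosing the model by a baseline test, or the effect measure by a pretest.

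**Conclusion.** The point holds as a poor method that the article states, and it is worth correcting. The harm is an analysis not fixed in advance, an estimand that can change with the data, and forgone precision.

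The size is modest. Adjustment for baseline PSQI would cut variance by about 4–16%, making 90 analysed patients worth about 94–107. This assumes a baseline SD of about 1.4, a follow-up SD of 3.60 and slopes of 0.5–1. The narrow entry range makes larger gains unlikely. The true level of the literal rule is about 3–5%, depending on how prognostic baseline and strata are, which the documents do not give. A charge of inflated type I error would go beyond what the documents show.

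**What to change.** Prespecify one primary model, used whatever the baseline comparison shows: ANCOVA of the PSQI global score at one named time point (for example week 8, the end of treatment), with arm, baseline PSQI, gender and age as covariates. Report the adjusted mean difference with its 95% confidence interval.

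- Replace the normality and variance pretests with robust or unequal-variance standard errors, and keep a rank-based analysis as sensitivity only.
- Drop baseline significance tests as the trigger for adjustment.
- Label the within-arm paired tests as descriptive.

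The cost is a change of wording in the protocol or the SAP and a few degrees of freedom. No new data or patients are needed, since all the covariates are already collected.

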#### Inclusion criteria

Eligibility for participation requires each of the following criteria to be met:
Symptoms comply with both the *Guidelines for the Diagnosis and Treatment of Insomnia in China* formulated by the CSMC in 2017 and *Expert Consensus on Diagnosis and Treatment of Anxiety and Depression in General Hospitals* formulated by anxiety disorder cooperation group, Psychiatry Branch, CMA in 2012The occurrence of insomnia was 3 times (including) to 5 times per weekThe Pittsburgh Sleep Quality Index (PSQI) score was 7 to 11 [17], and the Hamilton Anxiety Scale (HAMA) score > 14 [18]Age 18–70 years at the time of enrolment (either sex)Have not received WAA or other similar treatmentsPrefer physical therapy rather than medicationSigned informed consent

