#### Non-acupressure wrist-ankle strap group

This group served as the control group. A portable WAA' point compression therapy device is selected. The inner compression component will automatically contract without compression, and it will be worn at the same position on both wrists. Wear it for 30 min before going to bed every day, and take it off at bedtime. 2 weeks as a course of treatment, four courses in total. The non-acupressure wrist-ankle strap compression device is shown in Fig. 6B.

After the patients are determined to participate in the study, a trained person will be responsible for guiding upper 1. Daily attendance on the smartphone app will be adopted to ensure that participants wear it every day. At the end of each course, the wearing condition of the strap will be followed up by telephone.

In addition, all patients will be given CBTI. CBTI has achieved widespread scientific recognition as an effective treatment for a wide variety of insomnias. This approach can effectively correct the wrong sleep cognition and inappropriate behavior factors of patients with insomnia [19]. The study adopts the treatment proposed by Michael L. Perlis in *Cognitive-behavioral treatment of insomnia: A session-by-session guide*, including stimulus control therapy, sleep restriction therapy, sleep hygiene education, and cognitive therapy [20]. The treatment is conducted systematically and requires therapist-patient dialogues every week (face-to-face or telephone-based dialogues), eight times in total, as a course of treatment. CBTI will be implemented by two professional therapists trained in clinical sleep medicine programs and had psychological qualifications.

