In this trial, the patients with mild insomnia prefer physical therapy rather than medication, and there is no high risk without other treatments. Therefore, it is ethically possible for us to include a control group that receives just CBTI. This trial is a rigorously designed randomized controlled, double-blind trial. The design of the non-acupressure wrist-ankle strap, the wrist-ankle strap instruction manual, and follow-up appointments ensure the accuracy of the blind method of this trial. To ensure the quality of this research, before the research officially starts, we conducted a pre-experiment first, consult experts and literature to optimize the test plan based on the pre-test situation, and submitted the study protocol to the medical ethics committee for review and approval; each stage of the trial has an independent researcher to supervise the subject and collect feedback in time; all the research participants, including researchers, receptionists, and data processors, will be trained to ensure the smooth implementation of the trial.

The study aims to provide evidence-based medical evidence for the prevention and treatment of insomnia by acupressure wrist-ankle strap and promotes WAA clinical application. The result of this trial is expected to confirm that the new type of acupressure wrist-ankle strap can significantly improve the sleep quality and anxiety disorder of patients, reduce the suffering of patients, and improve the quality of life; it can also shorten the latency to fall asleep, increase the total sleep time, reduce the number of arousals and duration, improve sleep efficiency; it can reduce ACTH, CORT, 5-HT, and NA in the peripheral blood of patients with insomnia, thereby improving sleep quality.

In view of the above considerations, this study intends to sort out and summarize the clinical data of the new type of acupressure wrist-ankle strap for mild insomnia patients with anxiety disorder in this research group and form a standardized treatment plan. A strictly designed randomized controlled study method will be used to compare the improvement of acupressure wrist-ankle strap and non-acupressure wrist-ankle strap on the patients, to verify its efficacy further and explore the possible mechanism of action, to enrich the treatment of insomnia, improve its clinical efficacy, and lay the foundation for the popularization and application of the acupressure wrist-ankle strap.

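### The within-arm before–after tests have the same 5% status as the between-group test, although CBTI in both arms means a significant fall in the strap arm is not evidence of a strap effect

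*Protocol article*

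**What the plan says.** The Statistical analysis section puts two kinds of comparison in one sentence. Between the arms it plans an independent-samples t test. Inside each arm it plans a paired t test, whose purpose and condition are given as "for comparison within each group after data meeting normal distribution test and homogeneity test of variance". Where those checks fail, the rank-based counterparts (Mann-Whitney U between arms, Wilcoxon signed-rank inside each arm) take over. The section closes with "All statistical tests will be conducted at a 2-tailed significance level of 5" per cent. It does not call the within-group tests descriptive, and it does not say which of the two comparisons decides efficacy.

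Three other places bear on how a within-group result can be read:

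- **Non-acupressure wrist-ankle strap group:** "In addition, all patients will be given CBTI", as eight weekly sessions. The same paragraph states that "CBTI has achieved widespread scientific recognition as an effective treatment for a wide variety of insomnias".
- **Inclusion criteria:** entry requires a PSQI of 7 to 11 and "the Hamilton Anxiety Scale (HAMA) score > 14". PSQI is the primary outcome scale and HAMA is a secondary one.
- **Discussion:** the trial is expected to confirm that the strap "can significantly improve the sleep quality and anxiety disorder of patients", and that it lowers ACTH, cortisol, 5-HT and noradrenaline. The following paragraph says that the acupressure and non-acupressure straps will be compared in order to verify efficacy.

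**The concern.** A paired test within the strap arm tests whether scores changed over time. It cannot say why. The protocol itself supplies reasons for change that have nothing to do with the strap. Every patient gets a co-treatment described as effective. Patients enter only if HAMA exceeds a lower bound, so later HAMA scores will tend to be lower through regression to the mean. The sham arm is there to remove these influences, and a p-value computed in the strap arm alone brings them back.

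Two misreadings are then open. One is to report a significant fall in the strap arm as an effect of the strap. The other is to report that the strap arm changed significantly and the sham arm did not, as if that were a test of the difference between arms. The Discussion invites the first, because its expected results are phrased as improvement in patients and reduction in hormones and not as a difference from sham. What is at stake is a secondary claim printed beside the randomised result, not the randomised result itself.

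**Working it through.** **1. The plan's own figure.** The Sample size section uses a difference of 8.625 − 6.125 = 2.5, SD 3.60, two-sided alpha 0.05 and power 0.90. The printed formula gives 2 × 3.60² × (1.96 + 1.28)² / 2.5² = 43.5, so 44. The exact noncentral t calculation gives 45 (power 0.903). Dropout: 45 / 0.80 = 56.25, so 57 per arm and 114 in total. The stated figures reproduce, and they are built on the between-arm difference.

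**2. Inputs for the within-arm check.** From the document: two-sided 5% and n = 45 per arm. Assumed, because the document does not give them: an SD of change of 3.0 to 3.6, and a PSQI fall D of 0.5 to 2 points shared by both arms. The strap effect is set to zero.

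**3. Paired test in the strap arm.** The noncentrality is D / (SD / √45) and the critical value is t(0.975; 44 df) = 2.015. For D = 1 and SD = 3.6 the noncentrality is 1 / (3.6 / 6.708) = 1.863, and the test is significant with probability 0.445. In the same way:

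| Shared fall D | SD 3.0 | SD 3.6 |
|---|---|---|
| 0.5 | 0.194 | 0.149 |
| 1.0 | 0.590 | 0.445 |
| 1.5 | 0.907 | 0.780 |
| 2.0 | 0.992 | 0.954 |

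**4. Between-arm test in the same scenarios.** In simulation (20,000 runs per scenario) it rejects about 5% of the time throughout, as it should when the strap adds nothing.

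**5. Strap arm significant, sham arm not.** With equal true change and independent arms, the probability is p(1 − p), where p is the entry in the table above:

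| Shared fall D | SD 3.0 | SD 3.6 |
|---|---|---|
| 1.0 | 0.242 | 0.247 |
| 1.5 | 0.085 | 0.171 |
| 2.0 | 0.008 | 0.044 |

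The pattern is commonest when the shared fall is moderate and nearly vanishes when it is large, because both arms are then significant.

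**6. Regression to the mean, HAMA.** The expected fall is (1 − r) × SD × φ(a) / (1 − Φ(a)), with a = (14 − mean) / SD. Assumed: SD 6, population mean 12 to 16, retest reliability r of 0.7 to 0.8.

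- Mean 12: a = 0.333, so 6 × 0.3774 / 0.3694 = 6.13. The fall is 0.3 × 6.13 = 1.84 (r = 0.7) or 0.2 × 6.13 = 1.23 (r = 0.8).
- Mean 16: a = −0.333, so 6 × 0.3774 / 0.6306 = 3.59. The fall is 1.08 (r = 0.7) or 0.72 (r = 0.8).

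The range is about 0.7 to 1.8 points.

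**7. Regression to the mean, PSQI.** The 7 to 11 window is bounded on both sides. With assumed SD 3, population mean 7 to 11 and retest correlation 0.6 to 0.8, the effect runs from a fall of about 0.6 to a rise of about 0.6, and is zero at a mean of 9. For PSQI the case therefore rests on CBTI and not on selection.

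**The case against.** The strongest reply is that the randomised comparison is planned, is named first, and is the sole basis of the sample size. No section says efficacy will be concluded from a paired test, and the Discussion also says the two straps will be compared to verify efficacy. All of that stands. A reader might infer that the trial will judge the strap by its before–after change, or that the primary comparison is missing or invalid. The document supports neither. Nothing in it makes the paired tests subordinate, however, and that narrower gap remains.

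A second reply concerns the percentages. A reader might take 45–59% or 95–99% as a false-positive rate inflated from 5%. It is not: if PSQI truly falls by 1 or 2 points, the paired test is right to detect it, and these figures are its power. The error enters only when the change is credited to the strap. This objection stands, and the figures should be read that way.

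A third reply is that a significant result in the strap arm cannot simply be called expected under no strap effect, because the shared fall is not stated. This also stands. The only control figure is the pilot mean of 8.625, which lies inside the 7 to 11 window, and no pilot baseline is given. If the baseline had been 9 (assumed), the fall would be 0.375 and the paired test would be significant in only about 10–12% of trials at SD 3.6 (n = 45 to 57). That is still above 5%, but far from certain.

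**Conclusion.** The point holds in a limited form. The plan gives within-arm tests the same unqualified 5% status as the randomised comparison, in a trial where all patients receive an effective co-treatment and HAMA is selected on one side. A significant strap-arm change is then not evidence of a strap effect. How often it would arise without one depends on the shared PSQI fall: about 15–19% of trials at 0.5 point, 45–59% at 1 point and 95–99% at 2 points, with n = 45 and an assumed SD of change of 3.0 to 3.6. The misleading contrast of a significant strap arm with a non-significant sham arm occurs in about 24–25% of trials at 1 point, 9–17% at 1.5 and 1–4% at 2. These rates were worked out for PSQI only and should not be carried over to every scale.

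The design, the sample size and the primary contrast are unaffected. The correction is worth making because it closes a route to a misleading supplementary claim.

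**What to change.** In the Statistical analysis section, remove the paired t and Wilcoxon signed-rank tests within groups. Report within-arm change descriptively, as mean and SD. Add one sentence saying that efficacy on every outcome (PSQI, HAMA, actigraphy, hormones, TCM syndrome score) is judged on the between-group difference with its 95% confidence interval. In the Discussion, reword the expected-result sentence so that improvement and hormone reduction are stated relative to the non-acupressure strap, in line with the comparison described in the paragraph after it.

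The cost is wording only. There are fewer tests to run, the descriptive change is still reported, and neither trial conduct nor sample size changes.

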**Discussion:**

The results of this study will confirm the efficacy of acupressure wrist-ankle strap in treating mild insomnia patients with anxiety disorder and whether its mechanism is related to the HPA axis. The acupressure wrist-ankle strap may become a pure physical, no side effect treatment of mild insomnia.

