#### Primary outcome

The primary outcome is the Pittsburgh sleep quality index (PSQI) global score, which evaluates a patient's general sleep quality in the past month. The PSQI consists of 19 self-assessment questions and 5 questions assessed by sleep partners. Only 19 self-assessment questions will be scored. The 19 self-assessment questions constitute seven factors from 0 to 3 points. The cumulative score of each factor component is the total score of the PSQI. The total score ranges from 0 to 21. A higher score means worse sleep quality [21]. The PSQI will be assessed at baseline, 4, 8 weeks after randomization and follow-up period.

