#### Secondary outcomes

##### PSQI component scores

The PSQI component scores include seven domains, using 0, 1, 2, and 3 points to evaluate the patient's duration of sleep, sleep disturbance, sleep-onset latency, daytime dysfunction due to night sleep, sleep efficiency, need for medications to sleep, and overall sleep quality [17], which will be assessed at baseline, 4, 8 weeks after randomization and follow-up period.

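### All 16 secondary endpoints are tested at an unadjusted two-sided 5%, yet the Discussion expects the trial to confirm benefit on several of them, so the risk of a false confirmed claim is well above nominal

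*Protocol article*

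**What the plan says.** Under Primary outcome the protocol article names one endpoint: "The primary outcome is the Pittsburgh sleep quality index (PSQI) global score". The Sample size section rests on that score alone.

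The Secondary outcomes section lists the seven PSQI components ("The PSQI component scores include seven domains, using 0, 1, 2, and 3 points"), HAMA, three main actigraphy parameters (sleep efficiency, total sleep time, wake after sleep onset), four blood markers (ACTH, CORT, 5-HT, NE) and the TCM syndrome score. On timing, laboratory tests aside, "the primary and other secondary outcomes are detected at baseline and every four weeks". The blood markers have one post-baseline measurement, at week 8.

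The Statistical analysis section gives the method, "We will use an independent sample *t* test for comparison of between-group comparison and paired sample *t* test for comparison within each group", with rank-based alternatives, and then the level: "All statistical tests will be conducted at a 2-tailed significance level of 5"%. It gives the secondary endpoints no order, adjustment or exploratory label.

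The Discussion then lists what the result is expected to confirm. It says the strap "can significantly improve the sleep quality and anxiety disorder of patients", adds gains in sleep latency, total sleep time, awakenings and sleep efficiency, and ends with "it can reduce ACTH, CORT, 5-HT, and NA in the peripheral blood of patients with insomnia, thereby improving sleep quality". The abstract says "The results of this study will confirm the efficacy of acupressure wrist-ankle strap" and, in the same sentence, covers whether the mechanism involves the HPA axis.

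**The concern.** Unadjusted secondary tests are usually tolerable when they are read as support for a single primary result. Here the text pairs a fixed 5% level for every test with language that treats several secondary outcomes as things the trial will confirm. Someone following the article as written could report a nominal p below 0.05 on HAMA, an actigraphy parameter or a hormone as confirmed. Nothing in the text ties such a claim to a significant PSQI result.

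At stake is what the trial may conclude about anxiety, objectively measured sleep and the HPA mechanism. The primary comparison is not affected. Fixing the visit for the primary endpoint would not settle this point, because the secondary family would still be uncontrolled.

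**Working it through.** **The plan's own figure.** The Sample size section gives means of 6.125 and 8.625 (difference 2.5), SD 3.60, z-values 1.96 and 1.28, and k = 1. The formula gives 2 × 3.60² × (1.96 + 1.28)² / 2.5² = 43.5 per group. The t-based version gives 44.6, hence the stated 45. Dropout of 20%: 45 / 0.8 = 56.25, hence 57 per group and 114 in total. The figure reproduces from the stated SD, and it concerns the PSQI global score only.

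**Counting the tests.** Endpoints: 7 PSQI components + 1 HAMA + 3 actigraphy + 4 blood markers + 1 TCM score = 16. The first, second, third and fifth groups (12 endpoints) are measured at week 4, week 8 and follow-up; the blood markers only at week 8. Between-group tests: 12 × 3 + 4 × 1 = 40. This assumes one follow-up visit, since the schedule figure is not shown; the stated 13-week duration fits that. The paired within-group tests are not counted.

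**Which endpoints carry the claims.** HAMA, the three actigraphy parameters and the four blood markers make 1 + 3 + 4 = 8 endpoints.

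**Error rate with no true effect.** The Discussion's claims have a direction, so the relevant event is a significant result favouring the strap, with probability 2.5% per test.

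- Independent tests: 1 − 0.975^k. For k = 8 this is 18.3%; for k = 16, 33.3%.
- Either direction, independent: 1 − 0.95^k. For k = 16 this is 56.0%.
- Equal correlation ρ between test statistics: 1 − E[Φ((1.96 − √ρ·X)/√(1 − ρ))^k], with X standard normal, for the favourable direction.

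The documents give no correlations, so a range is shown.

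| Family, one visit | ρ = 0 | ρ = 0.5 | ρ = 0.8 |
|---|---|---|---|
| 4 blood markers, favourable | 9.6% | 7.8% | 5.7% |
| 8 named endpoints, favourable | 18% | 13% | 8% |
| 16 endpoints, favourable | 33% | 19% | 10% |
| 16 endpoints, either direction | 56% | 37% | 21% |

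Over all 40 tests, the favourable figure is 64% if every test is independent. It is 31% to 44% with correlation 0.3 to 0.5 between endpoints and 0.5 to 0.7 between visits.

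Against 2.5% for one test, the 8-endpoint family is inflated about 7-fold at ρ = 0 (18.3 / 2.5), 5-fold at 0.5 (12.5 / 2.5) and 3-fold at 0.8 (7.9 / 2.5).

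**The case against.** The strongest reply has four parts.

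*Secondary multiplicity is normally left to the analysis plan.* That is true, and neither that plan nor the full protocol is shown. Silence alone would not be a finding. But the article is not silent: it sets the level for all tests, and it attaches confirmatory language to secondary outcomes. That pairing stands in the text.

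*A hierarchy is already implied.* One outcome is labelled primary, the rest secondary, and the size rests on the primary. This also stands. A reader might infer that the protocol means to claim a secondary benefit whatever the PSQI result shows. It does not say so; it merely does nothing to prevent it.

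*The confirmatory wording is soft.* The Discussion states an expectation and not a decision rule. The abstract's firm statement concerns efficacy overall and leaves the mechanism as an open question. The abstract's methods paragraph and the Study design section speak of a possible mechanism, Study design describes the aim as exploring efficacy, and the Discussion later says the mechanism will be explored. So the documents do not flatly promise confirmation on hormones; their wording is uneven.

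*The error rates can be overstated.* A reader might infer from the 56% for 16 endpoints, or a larger figure for 40 tests, that a false confirmed claim is more likely than not. Those figures count results in either direction, assume independence, and include PSQI components and the TCM score, which the anxiety, actigraphy and hormone claims do not rest on. The PSQI medication component may also be almost constant, since recent hypnotic users are excluded; dropping it leaves about 15 endpoints and 37 tests. Read literally, the hormone claim is that all four markers fall. All four being falsely significant in that direction has a chance of about 0.5% or less at the correlations shown. These corrections are accepted in the verdict.

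**Conclusion.** The point holds as a substantially inflated risk of a false confirmed secondary claim. For the eight endpoints behind the anxiety, actigraphy and hormone claims, at one visit, the chance of at least one false positive favouring the strap is about 18%, 13% and 8% at correlation 0, 0.5 and 0.8, against 2.5% for a single test. For all 16 endpoints it is about 33%, 19% and 10%. That a false claim is likely is not established.

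These figures rest on no true effect on any endpoint, equal correlations chosen by assumption, and a claim being made when at least one endpoint is significant. The count of about 40 tests further assumes one follow-up visit. The PSQI global comparison and the sample size of 114 are untouched, so the matter is one to correct but not one that undermines the trial.

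**What to change.** In Statistical analysis, state that the PSQI global score at one prespecified visit is the only confirmatory test. State that all secondary endpoints and visits are exploratory and will be reported as between-group differences with 95% confidence intervals, with no claim of confirmation.

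If the sponsor wants a secondary claim to be confirmatory, for example on HAMA or the blood markers, name the endpoint and one visit, test it only after a significant primary result, and use a fixed order or Holm adjustment. Which secondaries to promote, if any, is the sponsor's choice; the documents do not rank them. The primary visit must be named for such a gate to be defined.

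In the Discussion, and in the abstract's wording on mechanism, change *confirm* to *explore* for secondary outcomes, in line with the exploratory language already used elsewhere in the article.

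The cost is a few sentences, with no added patients, visits or data. The downside is that a nominal p below 0.05 on a secondary endpoint can no longer be presented as confirmed.
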